### Study endpoints and statistical assessments

The primary endpoint is the safety of oral tricaprin for 52 weeks, as determined by analysis of the occurrence rate of adverse events, specifically the following: (i) MACE incidence; MACE includes cardiovascular death, nonfatal myocardial infarction, and nonfatal stroke.; (ii) AAA exacerbation; adverse events related to AAA exacerbation include nonfatal acute abdomen with proven AAA rupture, nonfatal acute abdomen without overt AAA rupture, a sudden change in skin color, or edema of the lower limbs with severe pain, and an abrupt need for surgical intervention; and (iii) unpredictable tricaprin side effects; unpredictable tricaprin side effects include miscellaneous events presumably related to tricaprin use and not attributable to (i) or (ii). These events will be assessed via physical examinations, vital sign assessments, safety laboratory tests, physiological tests, and abdominal CT scans. In particular, for MACE, AAA exacerbation, and unpredictable side effects following administration of tricaprin, the number of occurrences and events and their percentages will be calculated and presented, apart from the total analysis of all adverse events, owing to their clinical importance. Additionally, vital sign measures and laboratory test results will be summarized with descriptive statistics at each visit as a subanalysis. Vital signs include the following: systolic blood pressure (mm Hg); mean blood pressure (mm Hg, calculated using the formula [diastolic pressure + (systolic – diastolic) / 3”]; and heart rate (beats per minute). Laboratory test results will include measures of levels of alanine aminotransferase, gamma-glutamyl transpeptidase, blood urea nitrogen, creatinine, sodium, potassium, chloride, D-dimer, C-reactive protein, and brain natriuretic peptide; a complete blood cell count (white, red, hemoglobin, hematocrit, and platelets); and estimated glomerular filtration rate.

We will evaluate AAA diameter, volume, Agatston score, and AAWCV as secondary endpoints. Data will be summarized using descriptive statistics and compared at each time point. For MMSD and AV, changes during the first 6 months post–tricaprin administration and the final 6 months prior to study completion will be calculated and summarized using descriptive statistics. The Agatston score will be analyzed by stratifying AV changes into 3 groups, as follows: progression, no change, and regression. No interim analysis will be conducted, and missing data will not be imputed. Primary and secondary endpoints are listed in Table 3.

**Table 3 tbl3:** Primary and secondary outcomes

Primary (safety) outcome
• All adverse events
Additionally, the following items are to be collected, because of their clinical significance:
(i) MACE (cardiovascular death, nonfatal cardiac infarction, and nonfatal cerebral stroke);
(ii) adverse events related to AAA exacerbation (nonfatal acute abdomen with proven AAA rupture, nonfatal acute abdomen without overt AAA rupture, sudden skin color change or edema of lower limbs with severe pain, and abrupt need for surgical interventions); and
(iii) unpredictable side effects presumably related to tricaprin use (miscellaneous events that cannot be attributed to (i) and (ii).

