### Study population

This study will include individuals aged 50-85 years who have a diagnosed small AAA under conservative follow-up treatment and will provide written informed consent. Eligible participants must have evidence of having a AAA with a maximum minor short-axis diameter (MMSD) of ≤ 45 mm on a contrast-enhanced CT scan performed within 5 weeks before or 8 weeks after they provide consent. All eligibility assessments will follow participant provision of informed consent. A total of 10 individuals will be included. Exclusion criteria include having any of the following: a prior aortic repair (endovascular or open); surgery for AAA scheduled for within a year; dissecting or severely calcified AAA; or an estimated glomerular filtration rate of < 30 mL/min. A complete list of eligibility criteria is provided in Table 1.

**Table 1 tbl1:** Eligibility criteria

Inclusion criteria
• Aged 50–85 years at the time of consent
• Patients diagnosed with infrarenal AAA with a diameter of 30–45 mm according to enhanced CT scanning∗
• Provision of written informed consent directly from the patients

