### Sample size calculation and statistical considerations

A sample size of 10 participants was selected based on ethical considerations and the exploratory nature of the study. Although medium-chain triglycerides have a well-established safety profile, the safety of tricaprin in patients with AAA remains unverified. Moreover, including many participants in an initial safety assessment trial is unethical. AAAs are clinically diverse, with varying progression rates, and no established efficacy endpoints. Although MMSD is used frequently, sometimes it may not increase over extended periods.^35^ This variability makes the establishment of its clinical significance challenging. Given these factors and the lack of spontaneous reverse remodelliing in AAAs, we have opted not to perform statistical significance tests. Instead, we will summarize our findings using descriptive statistics.

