### Agatston score as an indicator of histologic reversibility

For exploratory purposes, we plan to evaluate AAA calcification. Previous studies have suggested a relationship between aortic aneurysms and calcification scores, showing associations with cardiac event risk^41^ and accelerated AAA expansion risk.^42^ However, debate remains regarding whether severe calcification worsens rupture rates or expansion speeds, challenging the notion that it should be considered a candidate for efficacy validation on its own. We predict that as an aneurysm becomes more calcified, its plasticity decreases, making regression detection less likely and resulting in minimal improvement in the lower CT value fraction of the AAWCV. Therefore, we intend to compare the Agatston scores before and after the intervention to determine whether these scores reflect the histologic alterations and reversibility of AAA. Evaluating trends in quantitative vascular calcification scores across the 3 groups, particularly in the “regression” group, is important as a predefined endpoint. Additionally, concurrently analyzing the favourable changes in AAWCV (with a reduction in low CT value regions) and decreases in the Agatston score may provide insights into the relationships among changes in adipocyte-rich, ischemic, and calcified regions within the aortic wall. Therefore, assessing the Agatston score across these 3 groups could guide the indirect histologic evaluation of AAA.

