### Study limitations

This study has 4 major limitations. First, we will use a small sample size and a short evaluation period to ensure the safety of the participants. A control group will not be included because of the lack of effective AAA treatments and the rarity of spontaneous regression.^43^ Thus, discussions on direct effectiveness based on trial results are complicated. Caution should be taken when discussing efficacy, particularly if AAA reverse remodelliing is observed, aside from its significant clinical impact. Moreover, to minimize the risk of withdrawal, at the eligibility assessment phase, we will estimate aneurysm diameter progression during this trial based on AAA growth rates from available data over the past 2-3 years. We also will assess high-risk findings for aortic dissection, such as ulcer-like projections, and confirm primary or secondary prevention of ischemic heart disease before enrollment. We will use these factors to guide the selection for reducing dropout rates. Furthermore, although aiming to identify efficacy endpoints with a small sample size of 10 patients may seem ambitious, prior studies lack established methods for evaluating efficacy, as no cases of aortic aneurysm regression have been observed with interventions. Additionally, the absence of a standard of care prevents determination of a clinical efficacy rate, complicating the calculation of the sample size required to demonstrate statistical significance. Given the rarity of annual hard event rates,^44^ efficacy evaluations cannot proceed without aneurysmal regression being achieved first through an intervention. Therefore, this study has not been designed to demonstrate efficacy but rather to serve as a foundation for larger clinical trials. In addition, a post-treatment follow-up protocol has not been established because the short half-life of tricaprin in humans (< 2 h) makes long-term adverse events from its accumulation unlikely. Indeed, no adverse events have been reported in AAA animal models treated with tricaprin, and the product has already been marketed in Japan without serious safety concerns. Therefore, extending the follow-up period beyond the clinical study period is unlikely to yield additional valuable information regarding tricaprin safety.

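### The Agatston score is related to aneurysm volume change only through three groups in 10 patients, with weight on a regression group that may be nearly empty; patient-level plots would use everyone

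*Protocol article*

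**What the plan says.** The protocol article, under Study endpoints and statistical assessments, lists the Agatston score as a secondary endpoint. All secondary endpoints are to be described and compared at each time point. One further analysis is specified for this score: "The Agatston score will be analyzed by stratifying AV changes into 3 groups", namely progression, no change and regression.

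The discussion section on the Agatston score as an indicator of histologic reversibility gives two purposes:

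- A prediction that "as an aneurysm becomes more calcified, its plasticity decreases, making regression detection less likely". Here calcification comes first and volume change is the outcome.
- A before-and-after comparison of the score, to see whether it reflects histologic change and reversibility. Here the score is a candidate marker.

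The same section says what matters as a predefined endpoint: "Evaluating trends in quantitative vascular calcification scores across the 3 groups, particularly in the" regression group.

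Study limitations describes spontaneous regression as rare and states that "no cases of aortic aneurysm regression have been observed with interventions". Study population fixes the number: "A total of 10 individuals will be included". The sample size section gives its basis, "A sample size of 10 participants was selected based on ethical considerations and the exploratory nature of the study", and rules out significance tests. Missing data are not imputed.

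**The concern.** The group that carries most of the interpretive weight is the one the article itself gives least reason to expect. With 10 patients or fewer, a rare category may hold nobody or one person, and a trend across three groups then says little about the relation of interest. Two patients with quite different volume changes also count alike once they share a group.

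The plasticity prediction concerns a graded relation: more calcification, less shrinkage. That can be looked at in every patient, whether or not anyone is classed as regressing. A table that describes the score within volume groups shows it only indirectly.

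At stake is how much the trial can offer the larger studies it is meant to prepare for. No safety conclusion is involved.

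**Working it through.** **Inputs from the article.** N = 10, set on ethical and exploratory grounds, so there is no calculated figure to reproduce. Three groups by AV change. No regression rate is stated; the nearest statements are that spontaneous regression is rare and that none has been seen with interventions.

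**Assumption.** Let p be the chance that a patient is classed as regression. It is varied because the article gives no value.

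**Step 1: size of the regression group.** With n patients,

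P(empty) = (1 - p)^n and P(at most one) = (1 - p)^n + n p (1 - p)^(n-1).

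At n = 10 and p = 10%: 0.9^10 = 0.349, and 0.349 + 10 × 0.1 × 0.9^9 = 0.349 + 0.387 = 0.736.

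| Assumed p | Empty, n = 10 | At most one, n = 10 | At most one, n = 8 |
|---|---|---|---|
| 2% | 82% | 98% | 99% |
| 5% | 60% | 91% | 94% |
| 10% | 35% | 74% | 81% |
| 20% | 11% | 38% | 50% |
| 30% | 3% | 15% | 26% |

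The n = 8 column assumes that two patients have no evaluable AV change. The chance of at most one patient passes 50% when p is below about 16% (n = 10) or about 20% (n = 8).

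**Step 2: any thin group.** In a multinomial simulation with n = 10, at least one of the three groups holds 0 or 1 patient in about 31% of trials when the groups are equally likely. With assumed shares of 60/30/10% for progression, no change and regression, it is about 79%.

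**Step 3: information lost by grouping.** Assume AV change is normal and give each group its mean as score. The share of variance kept is the sum over groups of (group probability × squared group mean in SD units).

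- Equal thirds: cut points at ±0.431, outer means ±1.091, middle mean 0. Kept: 2 × (1/3) × 1.091² = 0.79. Lost: about 21%.
- A 10/20/70 split: means -1.755, -0.861 and 0.497. Kept: 0.1 × 3.080 + 0.2 × 0.741 + 0.7 × 0.247 = 0.308 + 0.148 + 0.173 = 0.63. Lost: about 37%.

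**Step 4: precision of the alternative.** Approximate 95% interval for a rank correlation r on Fisher's scale: tanh[atanh(r) ± 1.96 × √((1 + r²/2)/(n - 3))].

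- n = 10, r = 0: 1.96/√7 = 0.741, tanh(0.741) = 0.63, so -0.63 to 0.63.
- n = 10, r = 0.5: -0.23 to 0.87.
- n = 10, r = 0.7: 0.04 to 0.93.
- n = 8, r = 0: -0.70 to 0.70.

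The signs mirror for a negative correlation. No cell can be empty, but the estimate stays imprecise.

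**The case against.** The strongest reply is that the planned analysis suits one of its two stated purposes. If the Agatston score is a candidate marker of reversibility, describing its change within groups defined by volume outcome is coherent. That stands. A reader might infer that the plan runs the hypothesis backwards; this is true only of the plasticity prediction, and a Spearman coefficient has no direction either.

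A reader might also infer that the regression group will almost surely be empty. The documents do not support that. They give no rate, what they say of past interventions is not about tricaprin, and the article calls tricaprin's effect uncertain. The AV cut-offs, which an article may leave to the full protocol, are not shown; if small falls counted as regression, measurement noise could fill the group.

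Nor does an empty group make the Agatston endpoint impossible to evaluate, since the time-point summaries need no grouping. And grouping does not discard most of the information: Step 3 shows that the larger part is kept.

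Finally, the article acknowledges the small sample and exploratory aim, and it excludes severely calcified aneurysms, which narrows the range over which any relation could appear. All of this stands and limits the point to an improvement in display. It is no reason to leave out a display that uses every evaluable patient.

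**Conclusion.** The point holds as a low-cost improvement to a descriptive secondary analysis; it is not an error in the plan. Beyond the time-point summaries, the score is related to volume only through three groups, with emphasis on one the article describes as rare. Under an assumed regression rate of 5% to 10%, that group has at most one of 10 patients with probability 91% to 74%. Once the assumed rate exceeds about 16%, such an outcome is no longer the more likely one. The loss of roughly 20% to 37% of the variance information in AV change rests on normality and on the two assumed splits. Patient-level display avoids both problems but cannot make 10 patients precise.

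**What to change.** Keep the three-group table and add two patient-level plots:

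1. Baseline Agatston score against percent AV change from baseline, for the plasticity prediction.
2. Change in Agatston score against AV change, for the before-and-after aim.

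Report Spearman's coefficient with a 95% interval beside each, stated to be descriptive and not a test. Draw the score on a scale that allows zeros, such as log(score + 1); this affects only the picture in the first plot, because ranks do not change. Mark each patient's group (progression, no change, regression) as a label on the points.

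The cost is one more descriptive analysis from data already being collected. Its drawback is a wide interval, so the text should say that it is exploratory. No visit, scan or sample size changes, and the primary safety analysis is untouched.

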**Figure 1 fig1:**
[figure not shown]
Trial scheme. The "pre-trial observation period" for screening before tricaprin administration shall not exceed 8 weeks. After tricaprin initiation, a 2-week follow-up period (initiation period) will follow, to rule out unexpected side effects. After initiation, patients will be monitored every 3 months and treated with tricaprin for 52 weeks. Contrast-enhanced computed tomography (CT) will be performed at the screening visit and visit 5, whereas unenhanced CT will be performed at the screening visit, visit 3, and visit 5.

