**Figure 2 fig2:**
[figure not shown]
Patient flowchart. The patient flowchart outlines the trial process. All participants who provide informed consent will undergo screening tests. Patients will be excluded if they are found to be ineligible based on screening, unable to tolerate the increase in tricaprin from 1.5 to 3.0 g/d, show concerning computed tomography (CT) findings at visit 3, experience severe adverse events, request withdrawal, or are deemed ineligible at any visit for other reasons. AAA, abdominal aortic aneurysm; MMSD, maximum-minor short-axis diameter After initiating tricaprin use at 3, ∗ After initiating tricaprin use at 3.0 g/d, the trial may be discontinued if any abnormal findings warrant cessation, even between scheduled visits.

**Table 2 tbl2:** Data collection schedule

Study item, data collection, or activity	Informed consent	Screening visit	Day 0	Day 1	Visit 1	Visit 2	Visit 3	Visit 4	Visit 5	Cessation
Day of performance, d	—	–56 to –1	0	1	14	91	182	273	364	—
Allowance period, d	—	—	—	—	± 7	± 14	± 14	± 14	± 14	+ 28
Informed consent	X	X	—	—	—	—	—	—	—	—
Patient’s background	—	X	—	—	—	—	—	—	—	—
Eligibility confirmation	—	X	—	—	—	—	—	—	—	—
Tricaprin administration, g	—	—	—	1.5	➡	3.0	➡	➡	➡	—
Adherence check	—	—	—	—	X	X	X	X	X	X
Comorbidities/Medical history	—	X	—	—	—	—	—	—	—	—
Abdominal contrast CT scan	—	X	—	—	—	—	—	—	—	X
Abdominal unenhanced CT scan	—	X	—	—	—	—	X	—	—	X
Clinical findings		X	X	—	X	X	X	X	X	X
Laboratory test		X	X	—	X	X	X	X	X	X
Electrocardiogram		X	—	—	—	—	—	—	X	X
Adverse events		—	—							

The shorter arrows indicate the same dosages as those shown on the left side of each one. The longer arrow represents the continuous monitoring of adverse events between visits.

CT, computed tomography.

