### Criteria for cessation of the protocol treatment

Tricaprin administration will be discontinued, and urgent surgical intervention will be considered if any of the following occur: aneurysmal diameter increases by ≥ 5 mm over a 6-month period or MMSD exceeds 51 mm on CT scans asymptomatically; AAA-related abdominal symptoms develop; or imaging evidence suggests impending rupture, even without symptoms. The need for urgent surgical intervention will be assessed in all patients who meet these criteria. However, participants meeting these criteria may opt to continue tricaprin use until the day of surgery.

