### Determination of the target for data analysis

The full analysis set will be used for data analysis, including all patients, excluding ineligible cases, with at least one tricaprin administration of 3.0 g/d and visit, regardless of treatment discontinuation during the follow-up period. A sensitivity analysis of secondary endpoints will be scheduled for participants with good compliance to medication use, defined as a tricaprin consumption rate > 60%. This threshold is based on phase 2a trial data,^29^ which showed that patients with triglyceride deposit cardiomyovasculopathy who maintained a tricaprin intake of ≥ 1.5 g/d showed improved clinical outcomes. If participants consume > 60% of tricaprin throughout the trial period, they will have ingested an average daily dose exceeding 1.8 g/d. Therefore, individuals in the sensitivity-analysis group should be considered to have received a dose sufficient to assess tricaprin efficacy.

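### The 52-week and final-6-month diameter and volume summaries can lose fast-growing aneurysms, and the article disagrees with itself on whether a stopped patient has a final scan

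*Protocol article*

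**What the plan says.** All places are in the protocol article.

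- **Study endpoints and statistical assessments:** "No interim analysis will be conducted, and missing data will not be imputed". Maximum minor short-axis diameter (MMSD) and aneurysm volume (AV) are compared at each time point. Their changes are also summarised separately for the first and the final six months. AV change is divided into progression, no change and regression, and the Agatston score is analysed by those groups.
- **Criteria for cessation of the protocol treatment:** "Tricaprin administration will be discontinued, and urgent surgical intervention will be considered if any of the following occur". The triggers include growth of at least 5 mm in 6 months and MMSD above 51 mm.
- **Determination of the target for data analysis:** the full analysis set keeps patients "regardless of treatment discontinuation during the follow-up period".
- **CT schedule in the text:** the Figure 1 legend says "Contrast-enhanced computed tomography (CT) will be performed at the screening visit and visit 5" and places unenhanced CT at screening, visit 3 and visit 5. Treatment protocol and study assessments, and Performance and measurements of CT scanning, agree. None of the three names a scan at cessation.
- **CT schedule in Table 2:** the row "Abdominal contrast CT scan" is marked at screening and under Cessation, with a dash at Visit 5. The unenhanced row is marked at screening, Visit 3 and Cessation, again with a dash at Visit 5.
- **Figure 2 legend:** concerning CT findings at visit 3 and severe adverse events are among the reasons for excluding a patient.
- **Sample size calculation and statistical considerations:** "A sample size of 10 participants was selected based on ethical considerations and the exploratory nature of the study", and "we have opted not to perform statistical significance tests". No dropout rate is given. Study limitations says only, of expected growth and other risk findings, "We will use these factors to guide the selection for reducing dropout rates".

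**The concern.** The rule that ends treatment, and may lead to repair, reads the same measurement that the secondary analysis summarises. A repaired aneurysm has no native diameter or volume to measure at visit 5. With no imputation and no stated use of the last available scan, such a patient stays in the full analysis set by name but adds nothing to the 52-week value, the final-6-month change or the AV groups. The missing values would come mainly from patients with growth, so what remains would look more stable than the treated group was.

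The study is uncontrolled, has ten patients and is meant as a foundation for larger trials. The Discussion gives particular weight to trends in the regression group. One or two absent fast growers could colour that reading. Whether they are absent depends on two things the article states in conflicting ways: whether a stopped patient is scanned, and whether that patient remains in the analysis.

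**Working it through.** **1. Is the missingness tied to the endpoint?** Entry is limited to 30–45 mm. A patient admitted at the upper limit passes 51 mm only after growing more than 51 − 45 = 6 mm. Both diameter triggers are therefore growth triggers. Visit 3 (day 182) is the only scheduled scan between screening and visit 5, so it is the scheduled point at which growth can cause a stop.

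**2. Which summaries lose such a patient?**

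| Summary | Patient stopped on the visit 3 scan |
|---|---|
| First-6-month MMSD and AV change | Contributes, if the full analysis set definition governs |
| Final-6-month change | Missing if repaired before visit 5 |
| 52-week value | Missing, unless a cessation scan exists and is used |
| AV group based on 52-week change | As for the 52-week value |
| Primary safety outcome | Unaffected; AAA exacerbation and abrupt need for surgery are counted |

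**3. Does a final scan exist?** Both CT rows of Table 2 have all ten cells, the visit 3 mark is in the expected column, and the electrocardiogram row marks Visit 5 and Cessation separately. As read, the table schedules CT at cessation and none at visit 5, and the text says the reverse. If the marks belong under Visit 5 and there is no cessation scan, the last scan of a patient stopped at visit 3 is the visit 3 scan.

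**4. Size.** The sample size of 10 has no formula behind it, so there is no planned figure to reproduce. All growth values below are assumptions. Let k of 10 patients stop at visit 3 at exactly +5 mm, and let the others grow m mm per 6 months.

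- Completer mean at 52 weeks = 2m
- Mean with the last scan included = [(10 − k) × 2m + 5k] / 10
- Gap = k(5 − 2m) / 10

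For k = 1 and m = 0.5: completers 2 × 0.5 = 1.0 mm; with the last scan (9 × 1.0 + 5)/10 = 1.4 mm; gap 0.4 mm.

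| m (mm per 6 months) | Completers | Last scan, k = 1 | Gap | Last scan, k = 2 | Gap |
|---|---|---|---|---|---|
| 0 | 0 | 0.5 | 0.5 | 1.0 | 1.0 |
| 0.5 | 1.0 | 1.4 | 0.4 | 1.8 | 0.8 |
| 1.0 | 2.0 | 2.3 | 0.3 | 2.6 | 0.6 |
| 1.5 | 3.0 | 3.2 | 0.2 | 3.4 | 0.4 |

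**5. How likely is it?** Assume normal 6-month growth with mean μ of 0.5 to 1.5 mm and SD σ of 1.0 to 2.0 mm. The chance of a visit 3 stop per patient is p = 1 − Φ((5 − μ)/σ), which runs from 0.0% to 4.0%. The chance of at least one stop in ten is 1 − (1 − p)^10, from 0% to 34%. Expected 12-month means:

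| μ, σ (mm) | All patients | Completers | With stop scan |
|---|---|---|---|
| 1.0, 2.0 | 2.00 | 1.89 | 1.98 |
| 1.5, 2.0 | 3.00 | 2.82 | 2.94 |

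At σ = 1.0 the three means do not visibly differ.

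**The case against.** A reader might infer that stopped patients have no later value and nothing replaces it, that the results describe only aneurysms that behaved well, or that every secondary endpoint is biased. The article does not support these readings:

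- Table 2 as read schedules both CT types at cessation.
- The full analysis set keeps discontinued patients, and a patient stopped on the visit 3 scan contributes to the first-6-month change.
- Surgery is considered, not certain, and nothing says that imaging ends when tricaprin does.
- Stops for adverse events need not reflect growth.
- No direction of bias is shown for the Agatston score or the aneurysm-wall CT values.
- Poor aneurysm outcomes are counted in the primary safety outcome.

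All of this stands, and it narrows the point.

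The size is also open to challenge. The one-patient example is chosen, and its 0.4 mm gap is smaller than the 0.8 mm per year that Study limitations places within measurement variability. The outcomes are exploratory and untested, and the article says the study was not designed to show efficacy. This limits how much the point matters. It does not remove it: measurement error scatters both ways, whereas loss of fast growers shifts the mean in one direction, and one patient is a tenth of the AV grouping.

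Finally, which scan feeds a descriptive table is often left to the analysis plan, which is not at hand. But the article itself states the no-imputation rule, and the conflicts over scans and exclusions lie within the article.

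**Conclusion.** The point holds in a limited form. Growth-triggered stopping with no imputation can make the 52-week and final-6-month MMSD and AV summaries, and the AV groups, informatively missing, with a lean toward stable aneurysms. The first-6-month change and the primary safety outcome are not affected in this way, provided the full analysis set definition, and not the Figure 2 exclusion, decides who is analysed.

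If one patient in ten is stopped at +5 mm, the completer mean is too favourable by 0.2 to 0.5 mm. With two it is 0.4 to 1.0 mm. The chance of any such stop at visit 3 is 0% to 34% under the assumed growth distributions, and the expected shift is at most about 0.18 mm (3.00 − 2.82). These figures rest wholly on assumed growth, because the article gives no growth distribution or dropout rate.

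The conflicts between Table 2 and the text, and between Figure 2 and the full analysis set, do not depend on any assumption. Displaced marks in the table text cannot be ruled out, so the printed table should be checked. If no cessation scan exists, the concern is stronger.

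**What to change.** 1. Reconcile Table 2 with the Figure 1 legend, Treatment protocol and study assessments, and Performance and measurements of CT scanning on CT at visit 5 and at cessation. Reconcile the Figure 2 legend with Determination of the target for data analysis on whether a stopped patient stays in the analysis.
2. For each full-analysis-set patient, summarise MMSD and AV change from screening to the last CT before any repair (visit 5, the cessation scan if one exists, or visit 3) and give its date. Assign the AV group from that scan.
3. Do not annualise. Doubling a 6-month change that was selected for crossing a threshold can overstate growth. Do not place every repaired patient in the progression group by rule either, since a stop can follow symptoms without measured expansion. List patients stopped for expansion, rupture or repair separately, by reason.
4. Show the completer summary alongside, with the number missing and why. The final-6-month change stays a summary of those with the scans to compute it, so it needs the same count.

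This needs no imputation model and no scans beyond those that the reconciled schedule contains. It costs a little more descriptive work, follow-up times in the last-scan summary will be unequal, and growth may look slightly less favourable.
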